## **Ethical Review Application Form for the Biomedical Ethics Committee of Anhui Medical University**

### **Key Points of the Research Proposal:**

#### **1. Research Background**

Gastric cancer is the third most prevalent cancer in China, with chemotherapy serving as a primary postoperative adjuvant treatment. This treatment often causes significant psychological and symptomatic distress in patients. Resilience is a process where individuals under internal and external pressure tap into their cognitive abilities, capabilities, or psychological traits, and utilize internal and external resources to actively adjust and repair their mechanisms, focusing on positive psychological responses and the activation of internal potential in adversity. Therefore, intervention strategies aimed at enhancing patients' psychological resilience can improve their psychological coping skills, helping them use their own strengths to alleviate negative physical and psychological experiences.

Currently, research on resilience, both domestically and internationally, is still in the exploratory stage. Many resilience intervention programs lack a specific theoretical framework, are not based on evidence, and fail to consider the dynamic changes in resilience. Moreover, these interventions often overlook the interaction between multiple dimensions and their impact on patients' psychological resilience. In line with the "Healthy China 2030 Action Plan," this study, based on social-ecological systems theory and empirical research, explores comprehensive intervention strategies to enhance the psychological resilience of cancer survivors, thereby promoting their physical and mental health and improving their well-being.

The research team previously developed a resilience intervention program centered on protective factors, involving both patients and their families. Preliminary applications of this program have shown good feasibility, acceptability, and effectiveness. We now aim to conduct a large-scale clinical trial to further validate and refine the intervention program and to explore strategies for enhancing resilience through semi-structured interviews, ultimately summarizing the best evidence.

#### **2. Research Objectives and Expected Outcomes**

##### **2.1 Research Objectives:**

(1) To verify the effectiveness of a resilience intervention program based on protective factors for gastric cancer patients and conduct a process evaluation, dynamically assessing issues within the intervention program, refining and revising the program, and providing evidence for enhancing cancer survivors' resilience.

(2) To explore, through qualitative research, the experiences, opinions, and attitudes of cancer survivors and their stakeholders towards strategies for enhancing

resilience, providing references for strategy development.

(3) To summarize the best evidence for resilience enhancement strategies for cancer survivors, guiding the revision of existing strategies and the proposal of new ones to better achieve the goal of improving resilience in cancer survivors.

## 2.2 Expected Outcomes:

Completion of the research project, resulting in the publication of 1-2 papers.

## 3. Research Design and Methods

This study focuses on gastric cancer patients undergoing chemotherapy as the representative sample.

### 3.1 Empirical Research:

3.1.1 Research Setting: Oncology Department of a tertiary hospital in Anhui Province.

3.1.2 Research Period: From July 1, 2023, to June 30, 2026.

#### 3.1.3 Participants:

Inclusion Criteria:

(1) Patients diagnosed with gastric cancer through pathological examination.

(2) Age  $\geq 18$  years.

(3) Patients who have undergone their first gastric cancer surgery and plan to undergo chemotherapy at the research hospital, with follow-up conditions.

(4) Patients whose condition allows for participation, who have provided informed consent, and are cooperative.

(5) Patients with an expected survival period of more than six months.

Exclusion Criteria:

(1) Patients with communication and understanding impairments.

(2) Patients with other severe diseases.

(3) Patients with a history of psychological disorders or mental illness.

(4) Patients currently participating in other clinical studies.

Dropout Criteria: Patients who, for various reasons, do not complete the entire resilience intervention program.

3.1.4 Sampling Method: Convenience sampling.

3.1.5 Sample Size Calculation: Sample size was calculated using G\*Power software. Based on the pilot study results and the estimated effect size for the primary outcome measure, psychological resilience, and accounting for a 10% dropout rate, the final sample size is determined to be 196 participants, with 98 in the intervention group and 98 in the control group.

3.1.6 Data Management and Analysis: Data will be double-entered using Epidata 3.1, and analyzed using IBM SPSS 24.0 software. Statistical significance is set at  $P \leq 0.05$ . Quantitative variables with normal distribution will be compared using independent sample t-tests, while non-normally distributed variables will be analyzed using the Wilcoxon rank-sum test. Qualitative variables will be compared using the chi-square test.

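### Dropout is defined only as not completing the intervention programme, yet 10% is allowed for it in both arms and no analysis population is stated, so a completers-only intervention arm is left open

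*Combined protocol and SAP*

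**What the plan says.** Section 3.1.3 gives one dropout rule, and section 6.1 repeats it word for word: "Dropout Criteria: Patients who, for various reasons, do not complete the entire resilience intervention program". No version for the control group appears, and no definition of loss to follow-up or of a missed assessment.

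Section 3.1.5 sizes the trial "accounting for a 10% dropout rate", without splitting that rate by arm, and concludes that "the final sample size is determined to be 196 participants, with 98 in the intervention group and 98 in the control group".

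Section 3.1.6 lists the tests. It begins "Quantitative variables with normal distribution will be compared using independent sample t-tests" and adds the Wilcoxon rank-sum and chi-square tests and a 5% significance level. It does not say which patients enter the comparison or how missing scores are handled. Section 6.2 lets any participant withdraw at any time, without linking withdrawal to the dropout rule or to the analysis.

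**The concern.** The rule turns non-adherence into dropout. The visible text describes no programme for controls, so a control cannot sensibly meet the rule; read literally, every control would be a dropout. In neither reading does it work as a common rule for two arms.

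It also misses the loss that matters for the result: a resilience score that is absent, in either arm, for any reason. A patient who stops the programme but fills in the questionnaire has lost nothing needed for the comparison. A control who never returns has, but is not covered.

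The first objective in section 2.1 is to verify effectiveness. If the rule is followed and dropouts are set aside, the intervention mean comes from patients selected for staying the course, while the control mean does not. Where staying the course is related to resilience, the two means differ even if the programme does nothing. Scores that were never collected from non-completers cannot be recovered at analysis, so this has to be settled while follow-up is still possible.

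**Working it through.** **1. The plan's own figure.** From 3.1.5: 98 per arm, 196 in total, 10% dropout. Effect size, power and sidedness are not given, so the base sample size cannot be reproduced; only the dropout step can be checked.

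- Dividing by the retained fraction: 88 / (1 − 0.10) = 97.8, rounded up to 98. In total, 176 / 0.90 = 195.6, rounded up to 196.
- Multiplying up instead: 89 × 1.10 = 97.9, also rounded up to 98.

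Either way, about 88 or 89 evaluable patients per arm were intended, with the allowance made in both arms. A rule that only one arm can meet would instead leave about 98 × 0.9 = 88 intervention patients against up to 98 controls.

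**2. Size of the bias if non-completers are removed from the intervention arm only.** Model, with no true effect and outcome SD 1: each intervention patient has a latent standard normal completion propensity with correlation ρ to resilience, and the lowest fraction f is removed. Then

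- bias = ρ × λ, with λ = φ(z_f) / (1 − f);
- for f = 0.10, z_f = −1.2816, φ(z_f) = 0.1755 and λ = 0.1755 / 0.90 = 0.195.

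Only the 10% comes from the plan. One-arm removal and ρ are assumptions. Note that ρ refers to the latent propensity, so the correlation with observed staying or leaving is smaller.

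| ρ | Bias (SD) | Type I error, normal approximation (88 v 98) | Type I error, simulated t-test (20,000 replicates) |
|---|---|---|---|
| −0.3 | −0.3 × 0.195 = −0.06 | 6.8% | 7% |
| 0 | 0 | 5.0% | 5% |
| 0.3 | 0.3 × 0.195 = 0.06 | 6.8% | 7% |
| 0.5 | 0.5 × 0.195 = 0.10 | 10.3% | 11% |
| 0.7 | 0.7 × 0.195 = 0.14 | 16.0% | 17% |

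The error rates are two-sided at 0.05. At ρ = −0.3 the error rate is also raised, but the false effect runs against the programme.

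**3. Contrast: the same selection in both arms.** With equal loss by the same mechanism in each arm and no true effect, mean bias is about 0 and simulated type I error is 5–7%. The inflation in step 2 therefore depends on removal being one-sided.

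**4. Power cost of keeping non-completers.** Assume 80% power, two-sided 0.05 and 88 per arm, which implies d = 0.425. Neither the 80% nor the 0.425 is in the plan; across 80–95% power and one- or two-sided tests, the implied d runs from 0.376 to 0.546. If 10% of intervention patients get no benefit, the effect as allocated is 0.425 × 0.9 = 0.3825. With all 98 per arm analysed, power is 75.9%, against 80.1% for d = 0.425 with 88 per arm.

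**The case against.** The strongest reply is that nothing in the documents removes dropouts from the analysis. Section 3.1.6 is silent on who is analysed, and enlarging a sample for dropout does not fix an analysis set: plans that analyse everyone also allow for lost outcomes. The equal allowance in both arms suggests that the authors expected loss on both sides and drafted the definition loosely. This stands. A reader might infer that the trial will compare selected completers with all controls and is therefore biased in the programme's favour. The documents do not support that, because no section states the exclusion and section 6.2 lets controls withdraw too.

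The direction is also not given. It is plausible that patients who stop attending during chemotherapy are the more distressed ones, but the documents offer no data on this, and the sign depends on it.

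Finally, the text is incomplete. It is a key-points application, the flowchart in section 4 is not shown, one part was removed before review, and section 9 breaks off as it turns to data management. A rule on withdrawals, or a description of the control condition, could lie there.

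What the reply does not remove is the wording in view. The only dropouts defined are programme non-completers, the sample is enlarged to allow for dropouts, and the analysis section, which is present, says nothing that keeps them in. If the authors did expect loss in both arms, the definition contradicts the calculation.

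**Conclusion.** The point holds in conditional form. Two things are established from the text: the dropout rule fits one arm only and confuses adherence with loss of outcome data, and the sample size calculation applies a single rate to both arms. With no stated analysis population, a completers-only intervention arm is permitted and is a natural way to follow the rule, but it is not prescribed.

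If it happened at the plan's own 10% rate, the consequence would be modest to material: a false effect of about 0.06 to 0.14 SD and a type I error of about 7% to 17%, for latent correlations from 0.3 to 0.7. This rests on one-sided removal and on a positive correlation. The problem is more than missing detail, because a stated rule points the wrong way and its correction is cheap.

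**What to change.** - **3.1.3 and 6.1:** replace the dropout rule with two definitions. Programme non-completion is recorded as an adherence measure only; these patients stay in follow-up and complete the same questionnaires. Loss to follow-up is a missing resilience score at the primary time point, defined identically in both arms.
- **3.1.5:** state that the 10% is this loss to follow-up, in either arm.
- **3.1.6:** state that the primary analysis includes all patients in their allocated group, with a named missing-data method (a mixed model or multiple imputation is one option). Label any completers comparison as secondary.

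The cost is wording in these four sections and the effort of collecting questionnaires from patients who stop the programme. The estimate may be somewhat less favourable: under the assumptions in step 4 of the working, power is about 76% rather than 80%. Analysis as allocated removes the one-sided selection, but it does not by itself guarantee a 5% error rate. That also needs near-complete outcomes or a sound missing-data method, and comparable arms; the visible text does not describe how patients are allocated.

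### Sections 3.1.1 to 3.1.6 state no rule for assigning patients to the two groups of 98, and the planned unadjusted tests offer no protection if assignment turns out to be selective

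*Combined protocol and SAP*

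**What the plan says.** Objective (1) in section 2.1 is causal: "To verify the effectiveness of a resilience intervention program based on protective factors for gastric cancer patients". Section 1 announces a large clinical trial but does not call it randomised.

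On how patients are obtained, the whole content of section 3.1.4 is "Convenience sampling". Section 3.1.5 then fixes the total at "196 participants, with 98 in the intervention group and 98 in the control group". Nothing between these two statements, or elsewhere in 3.1.1 to 3.1.6, says how a recruited patient comes to be in one group rather than the other.

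Section 3.1.6 gives the analysis: "Quantitative variables with normal distribution will be compared using independent sample t-tests", while "non-normally distributed variables will be analyzed using the Wilcoxon rank-sum test"; categorical variables get a chi-square test. The threshold is P ≤ 0.05. No baseline value or other covariate enters any of these comparisons.

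**The concern.** A two-group comparison supports a causal claim if the groups were formed by chance, or if the analysis deals credibly with the ways in which they differ. The readable text secures neither.

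If the person enrolling also decides who receives the programme, patients who are more willing, fitter or better supported could be steered towards it. Those traits could plausibly go with higher scores on psychological resilience, which is the primary outcome. Some eligibility rules in 3.1.3 rest on judgement: whether the patient will cooperate, whether another disease counts as severe, whether the patient is well enough to take part. If the arm is known at enrolment, these rules can be applied differently in the two groups. An unadjusted t-test would credit any resulting difference to the programme. More patients would not help, because a larger sample only makes a biased estimate more precise.

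**Working it through.** **Step 1: the plan's own figure.** Section 3.1.5 gives 98 per group after allowing for 10% dropout. Working back, 88 / (1 − 0.10) = 97.8, rounded up to 98, and 2 × 98 = 196. So 88 evaluable patients per group fits the stated total. The full calculation cannot be reproduced, because the effect size, SD, power and sidedness are not given. With 88 per group and alpha 0.05, the detectable standardised difference is 0.425 (two-sided, 80% power). Across one- and two-sided tests at 80% to 95% power it runs from 0.376 (one-sided, 80%) to 0.546 (two-sided, 95%).

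**Step 2: where an allocation rule could stand.** The items of section 3.1 are numbered without a gap:

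| Item | Content | Allocation rule? |
|---|---|---|
| 3.1.1 | Setting | No |
| 3.1.2 | Period | No |
| 3.1.3 | Eligibility and dropout | No |
| 3.1.4 | Sampling | No; recruitment only |
| 3.1.5 | Sample size | Group sizes only |
| 3.1.6 | Data management and tests | No; no adjustment either |

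The remaining readable sections add nothing on a random sequence, concealment, or assignment by ward, period or preference. Section 4 consists of a flowchart whose figure is not shown.

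**Step 3: what selection would do to the test.** Suppose the programme has no effect and the groups differ by b SD on the outcome through selection alone. The values of b are assumptions; the documents give no basis for any particular value. The test is also assumed to be two-sided at 5%.

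- Standard error of the difference in SD units: √(2/88) = 0.151.
- Noncentrality: b / 0.151, with 2 × 88 − 2 = 174 degrees of freedom.
- False-positive rate: the probability that the noncentral t statistic falls outside the two-sided 5% limits.

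| b (SD) | Noncentrality | False-positive rate, 88 per arm | Same, 98 per arm |
|---|---|---|---|
| 0 | 0 | 5.0% | 5.0% |
| 0.1 | 0.66 | 10.1% | 10.7% |
| 0.2 | 1.33 | 26.1% | 28.6% |
| 0.3 | 1.99 | 50.8% | 55.2% |

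A normal approximation for b = 0.2 and 88 per arm agrees: 1 − Φ(1.96 − 1.33) plus a negligible lower tail gives 26.4%. The last column shows that the error grows with the sample. All three non-zero values of b lie below the whole range of detectable differences in step 1, so a bias too small to count as a target effect would still distort the test.

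**The case against.** The strongest reply is that sampling and allocation are different things. Convenience recruitment followed by random assignment is a common and valid design; the recruitment method limits generalisability, not the comparison between arms. This stands. Section 3.1.4 is not evidence of non-random allocation, it would not contradict a flowchart that shows randomisation, and consecutive enrolment is not needed for a valid comparison.

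Second, the text is incomplete. The flowchart is not visible, section 7 is absent and section 9 breaks off. A flowchart of the study process is a natural place to show assignment. This also stands, and it rules out two stronger conclusions that a reader might infer: that the trial is non-randomised, and that it cannot verify effectiveness. The documents support neither. If allocation is random and concealed, an unadjusted t-test of the groups as assigned is valid, and leaving out baseline costs only precision. A flowchart box marked as randomised would still not say who generates the sequence or how it is concealed, so written text would be needed in either case.

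Third, the selection differences are invented for illustration, and being smaller than a detectable effect does not make them likely. That is correct. They show how sensitive the test is, not how large the bias will be.

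**Conclusion.** The point holds in this form: the readable text gives no rule for assigning patients to the two groups, and the analysis has no adjustment to fall back on if assignment is selective. This goes beyond missing detail, because staff could choose the arm, comply with every readable sentence and still produce a confounded comparison.

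How serious it is depends on the sponsor's answer. If randomisation exists but is shown only in the flowchart, the remedy is to write it down in full. If it does not exist, the effectiveness objective is not supported by the planned tests. The illustrative error rates of about 10%, 26% and 51% rest on 88 evaluable patients per arm, a two-sided 5% test, no true effect, and assumed differences of 0.1, 0.2 and 0.3 SD.

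**What to change.** **Section 3.1: add an allocation item after 3.1.4.** Suggested content: once eligibility has been confirmed and the baseline questionnaire completed, patients are individually randomised 1:1 from a computer-generated list in permuted blocks of varying size. The list is held by an existing team member who does not enrol patients, and each assignment stays concealed until it is made. Convenience recruitment may remain.

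**Section 3.1.6: adjust the primary comparison for baseline resilience.** No readable section says that resilience is measured at baseline, so the sponsor should first confirm this.

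**If allocation is not random, or some patients were enrolled without it.** The research period in 3.1.2 opened on July 1, 2023, so enrolment may already have begun. In that case, call the study quasi-experimental, pre-specify adjustment for baseline resilience and for the prognostic factors actually collected, and reword objective (1) in section 2.1 as an association claim. Adjustment of this kind does not remove selection on unmeasured factors.

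**Cost.** A protocol amendment and a randomisation list, with no increase in the 196 patients. If resilience is not yet measured at baseline, one questionnaire is added. In the non-random case the further cost is a weaker stated conclusion.

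### Section 3.1.6 compares resilience between the groups with unadjusted two-group tests and names no baseline covariate; adjusting for baseline resilience would buy precision at almost no cost.

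*Combined protocol and SAP*

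**What the plan says.** Section 3.1.6 (Data Management and Analysis) holds the whole readable quantitative analysis plan. On continuous measures it says: "Quantitative variables with normal distribution will be compared using independent sample t-tests". Non-normal variables get a Wilcoxon rank-sum test and qualitative variables a chi-square test, with significance at 0.05. No covariate, ANCOVA, change score, repeated-measures model or group-by-time term is named, and no time point is given for the outcome comparison.

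Section 3.1.5 makes resilience the basis of the sample size: "Based on the pilot study results and the estimated effect size for the primary outcome measure, psychological resilience". It continues, "accounting for a 10% dropout rate", and ends: "the final sample size is determined to be 196 participants, with 98 in the intervention group and 98 in the control group". It gives no effect size, target power or sidedness.

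Section 3.1.4 says that patients are recruited by convenience sampling. The readable text does not say how they are then allocated to the two groups. It also does not state when resilience is measured. The flowchart in section 4 is not shown and section 9 breaks off in the text available.

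**The concern.** A patient's resilience score before the programme usually predicts the score after it. A test that leaves the earlier score out treats that predictable variation as noise, so the confidence interval is wider and the power lower than the same patients could give. It also lets part of any baseline difference between the groups pass into the estimated effect.

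Both matter for a trial whose first objective (section 2.1) is to verify that the programme works. A real but moderate benefit could be missed. A positive result could also be challenged if the groups happened to start apart, because the plan has no prespecified adjusted estimate to answer with.

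**Working it through.** **Inputs from the documents.** 98 per group, 10% dropout and significance level 0.05 (sections 3.1.5 and 3.1.6).

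**Assumptions.** Two-sided testing; equal SDs in the groups; a baseline-to-follow-up correlation r of 0.3 to 0.7. The documents give no value of r.

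**Step 1: the plan's own figure.** The dropout step is consistent: 88 / 0.9 = 97.8, rounded up to 98 per group, or 196 in total. The 88 itself cannot be reproduced, because effect size, power and sidedness are not given. Several input sets fit or nearly fit. For example, d = 0.5, one-sided, 95% power gives exactly 196; d = 0.5, two-sided, 90% power gives 192. The calculations below therefore start from 88 evaluable per group.

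**Step 2: precision.** By noncentral t, 88 per group and two-sided 0.05, the t-test detects 0.425 SD with 80% power and has 64% power for a true 0.35 SD. (The 0.35 SD is an illustration, not a figure from the plan.) ANCOVA multiplies the residual variance by (1 − r²), so the detectable difference becomes 0.425 × √(1 − r²). The gain in effective patients is 1/(1 − r²) − 1.

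| r | 1 − r² | Detectable difference at 80% power | Power at 0.35 SD | Worth in patients |
|---|---|---|---|---|
| no adjustment | 1 | 0.425 SD | 64% | – |
| 0.3 | 0.91 | 0.405 SD | 68% | +10% |
| 0.5 | 0.75 | 0.368 SD | 76% | +33% |
| 0.6 | 0.64 | 0.340 SD | 82% | +56% |
| 0.7 | 0.51 | 0.303 SD | 90% | +96% |

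**Step 3: an observed chance imbalance.** Under random allocation the baseline difference has standard error √(2/88) = 0.151 SD, so 95% of trials fall within about ±0.30 SD. An observed difference b shifts the unadjusted result by r × b. At b = 0.2 SD the shift is 0.06, 0.10 and 0.14 SD for r = 0.3, 0.5 and 0.7.

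Given b, the unadjusted difference has mean r × b and standard error 0.151 × √(1 − r²), while the t-test's critical value stays at 1.96 × 0.151 = 0.295. With no true effect the t-test therefore rejects in:

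| r | b = 0.2 SD | b = 0.3 SD |
|---|---|---|
| 0.3 | 5.7% | 8.0% |
| 0.5 | 6.8% | 13.3% |
| 0.7 | 7.4% | 21.4% |

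ANCOVA stays at about 5% in each cell. Averaged over all random allocations, the t-test also stays at 5%.

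**Step 4: groups that differ stably.** Suppose the groups differ by b at baseline for reasons that persist, and there is no treatment effect. The ANCOVA estimate is then off by b × (1 − r), with standard error 0.151 × √(1 − r²). For r = 0.5 and b = 0.3: 0.15 / 0.131 = 1.15 standard errors, so it rejects in 21%. For r = 0.7 and b = 0.2: 0.06 / 0.108 = 0.56, so 9%. Over r = 0.5 to 0.7 and b = 0.2 to 0.3 the range is 9% to 21%. The t-test, off by the whole of b, rejects in 26% (0.2 / 0.151 = 1.33 standard errors) to 51% (0.3 / 0.151 = 1.99).

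**The case against.** **The t-test is valid under randomisation.** This stands. It is unbiased on average and keeps 5% overall, so chance imbalance is a conditional problem. The precision loss remains.

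**The size rests on an assumed correlation.** This stands too. At r = 0.3 the gain is small: 0.425 to 0.405 SD, and 64% to 68% power.

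**The t-test might be applied to change scores.** The wording does not exclude it. However, the variance of a change score is 2(1 − r) times that of the follow-up score, which is 1.4 at r = 0.3. Power of 80% would then fall to 66%, and a 0.2 SD imbalance would leave a shift of −0.14 SD.

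**Stronger readings that the documents do not support:**

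- A reader might infer that the trial is not randomised and that ANCOVA would cure this. Convenience sampling describes recruitment, not allocation, and the flowchart is not visible. A null rejection rate of 10% to 28% for the t-test can be obtained with a systematic difference of 0.2 to 0.3 SD, but only if that difference regresses by r at follow-up. If it is stable, ANCOVA is biased as well (step 4).
- A reader might infer that the plan discards baseline and repeated scores it already holds. The readable text confirms neither.
- The background says that earlier programmes "fail to consider the dynamic changes in resilience". That criticises interventions, not statistical models, so it does not contradict section 3.1.6.
- Loss of patients with missing scores, or lack of an interval, might be held against the t-test in particular. ANCOVA also drops patients without a follow-up score, and a t-test does give a mean difference with a confidence interval.

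**Conclusion.** The point holds as a matter of precision and specification. The readable plan names no baseline covariate for its primary outcome, and adding one improves the analysis at every correlation examined: modestly at 0.3, substantially at 0.5 and above. The figures rest on 88 evaluable per group, two-sided testing and an assumed correlation.

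Protection against an observed chance imbalance is a second gain. It is negligible to modest at r = 0.3 and reaches the 7% to 21% range only at r = 0.5 to 0.7. If allocation is not random, adjustment lessens the bias from a baseline resilience difference but cannot be relied on to remove it, and it does nothing for unmeasured differences. None of this shows that 196 is wrong or that the planned test is invalid under random allocation. The change should be made, but the trial does not depend on it.

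**What to change.** In section 3.1.6, make the primary analysis of resilience an ANCOVA of the follow-up score on group and baseline score at one named time point. Report the adjusted mean difference with its 95% confidence interval, and treat other time points as secondary. If there are several follow-ups, use a linear mixed model with baseline score, group, time and group-by-time, and take the group contrast at the named time point as primary. The mixed model also keeps patients with partial follow-up.

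State in the protocol text how patients are allocated, so that a reader can judge what the adjustment can and cannot correct.

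If no baseline score is scheduled, give the same questionnaire once before allocation. The cost is a few lines of text and, at most, that one questionnaire. No extra patients are needed, and SPSS 24.0, already named in the plan, fits both models.

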#### 6.2 Protection Measures:

Participants will be informed of all relevant information about the study and its progress, allowing them to decide voluntarily whether to continue participating. Participants may withdraw from the study at any time without affecting their medical care or rights. If continuing in the study poses a significant risk, the study will be terminated. During the study, participants can report any discomfort to the research team.

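### The resilience comparison in 3.1.6 can use only patients with an observed score, and the 10% dropout allowance protects precision but not comparability if loss is related to resilience and differs between groups

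*Combined protocol and SAP*

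**What the plan says.** Section 3.1.6 lists double data entry, the software, a 0.05 significance level and three tests. For quantitative outcomes the first is: "Quantitative variables with normal distribution will be compared using independent sample t-tests". Non-normal variables go to the Wilcoxon rank-sum test and qualitative variables to the chi-square test. The section names no analysis set, covariate, missing-data method, sensitivity analysis or treatment of deaths.

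Dropout enters the planning only in 3.1.5, where the sample size is "Based on the pilot study results and the estimated effect size for the primary outcome measure, psychological resilience", and then, "accounting for a 10% dropout rate, the final sample size is determined to be 196 participants", split 98 and 98.

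Three other places bear on who may lack a score:

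- The inclusion criteria in 3.1.3 require "Patients with an expected survival period of more than six months".
- Section 6.2 says: "Participants may withdraw from the study at any time without affecting their medical care or rights". It does not say whether outcomes are still collected afterwards.
- Sections 3.1.3 and 6.1 define a dropout as someone who, for whatever reason, does not finish the whole programme. They do not say whether such patients remain in the analysis.

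**The concern.** A t-test or rank-sum test with no imputation or model behind it leaves out every patient without a follow-up score. The plan never calls this a complete-case analysis, but that is what it produces. For these unadjusted tests, the comparison is fair if having a score is unrelated to resilience, or if the resulting selection is the same in both groups.

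Neither condition can be taken for granted. The patients are on chemotherapy after gastric cancer surgery, and the protocol's background section itself describes chemotherapy as psychologically and physically distressing. A patient too unwell to answer may well be less resilient. One group has a programme to attend and the other has none described, so the reasons for leaving may differ.

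The first objective is to establish that the programme works. If the intervention group loses more of its less resilient patients, an ineffective programme can look effective. If the control group does, a real effect is diluted. Analysing every patient who has a score in the assigned group would not cure this, because the missing scores stay missing.

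**Working it through.** **1. The plan's own figure.** Effect size, SD, power and sidedness are not stated, so 196 cannot be fully re-derived. The dropout step is consistent: 88 / 0.90 = 97.8, rounded up to 98 per group (89 × 1.10 = 97.9 also gives 98). So 2 × 88 = 176 patients become 196. With 88 per group and two-sided 0.05 (assumed), the detectable effect is 0.425 SD at 80% power and 0.491 SD at 90%. The allowance secures that precision and does nothing else.

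**2. Bias formula.** Let a fraction p of a group lack a score, and let those patients average δ SD below the full-group mean μ. From (1 − p) × observed mean + p(μ − δ) = μ, the observed mean is μ + pδ/(1 − p). With no true effect, the difference between observed means is

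bias = δ × [p₁/(1 − p₁) − p₂/(1 − p₂)].

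**3. Inputs.** From the documents: 98 per group, level 0.05, and 10% as the overall figure. Assumed: the split between groups, and δ from 0.5 to 1.0. The rejection rate is from the noncentral t distribution with the observed group sizes. The standard error is √(1/n₁ + 1/n₂), which is 0.151 SD in both rows below.

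| Loss (group 1 v 2) | Observed n | p₁/(1−p₁) − p₂/(1−p₂) | Bias, δ = 0.5 | Bias, δ = 1.0 | False-positive rate |
|---|---|---|---|---|---|
| 15% v 5% | 83 v 93 | 0.1765 − 0.0526 = 0.124 | 0.062 SD | 0.124 SD | 6.9% to 12.9% |
| 12% v 8% | 86 v 90 | 0.1364 − 0.0870 = 0.049 | 0.025 SD | 0.049 SD | 5.3% to 6.2% |

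Against a detectable effect of 0.425 SD, the first row amounts to 15% to 29% (0.062/0.425 and 0.124/0.425).

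**4. Sensitivity to the definition of δ.** If the gap g is measured from the observed patients instead of the full-group mean, the bias is p₁g₁ − p₂g₂. At 15% v 5% this gives 0.05 SD (g = 0.5) and 0.10 SD (g = 1.0), with false-positive rates of about 6.3% and 10%. The message is the same.

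**5. When there is no bias.** Unequal rates with g = 0 give none. Equal rates (10% and 10%) with equal gaps give none. Equal rates with a 1 SD gap in one group only give 0.10 SD. So both the link to resilience and a difference in rate or type of loss are needed.

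**6. Does the remedy help?** In a simulation with loss driven only by baseline resilience (log-odds 1 per SD, baseline-outcome correlation 0.5 to 0.7, 15% v 5% loss, 4000 runs per setting), the observed-score comparison was off by about 0.05 to 0.06 SD. With baseline in the model it was off by 0.00. Loss that depends on later, unrecorded deterioration is not removed this way, hence the sensitivity analyses.

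**The case against.** **The size is conjecture.** The documents give no loss by group, no reasons, no death rate and no assessment times, and near-equal loss does almost no harm. This stands. The figures are illustrations, and the direction could be either way. A reader might infer that the trial will overstate the programme's effect; nothing in the documents supports that.

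**Frequent loss through death is not documented.** A reader might take the survival criterion to mean that patients are expected to live just over six months, so that scores will often be missing through deterioration or death. The criterion sets a minimum, not the expected survival of those enrolled. The same list asks for a condition that permits participation and excludes other severe diseases. Death as a cause of missing scores is a reasonable inference from the population, but its frequency is unknown.

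**The 10% is not a missing-score rate.** Dropout is defined by not finishing the programme, and some of those patients may still give a score. This stands, and the 10% is used above only as a convenient scale. Nor do the documents say that non-completers are removed from the analysis.

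**A rule may exist elsewhere.** The flowchart is not shown, the part between 6.2 and section 8 is not available, and section 9 breaks off at data entry. A rule there cannot be excluded. Section 3.1.6, where it belongs, reads as complete and has none.

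What survives is that the stated tests, followed as written, have no protection against selective loss.

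**Conclusion.** The point holds in conditional form. As written, 3.1.6 compares observed scores only, and 3.1.5 answers dropout only with numbers. Bias follows if patients without a score have lower resilience and the rate or type of loss differs between groups. Under the assumed 15% v 5% split with a deficit of 0.5 to 1.0 SD, it is 0.06 to 0.12 SD, with a false-positive rate of 7% to 13% in place of 5%. At 12% v 8% it is 0.02 to 0.05 SD and 5% to 6%. The true size and direction cannot be obtained from the documents.

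This is more than a missing detail, because a better and inexpensive method than the stated one is available. It should be changed before outcome data are examined, since a method chosen afterwards is open to selection.

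**What to change.** In 3.1.6, for psychological resilience:

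1. Make the primary analysis a linear mixed model (with baseline as one of the repeated scores, so that patients without a follow-up score still contribute) or multiple imputation including baseline resilience. Apply it to all 196 patients in their assigned groups, whether or not they finished the programme. Add other prognostic variables only where the trial already collects them.
2. Tabulate missing scores by group and reason, with deaths shown separately.
3. Report two sensitivity analyses. First, shift imputed scores by 0.5 and 1.0 SD, stating beforehand which group or groups are shifted (this needs imputation even if the primary analysis is a mixed model). Second, run a rank-sum test with deaths ranked lowest, labelled as a composite of resilience and survival. It is useful because a score after death does not exist and the primary model does not define one.

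The sensitivity analyses should not be a condition for claiming effectiveness. If a claim had to survive a 1.0 SD downward shift in the intervention group alone, an effect of 0.425 SD would fall to 0.325 SD with 10% imputed (0.425 − 0.10 × 1.0). Power with 88 per group would then fall from 80% to about 57%. With 15% imputed the figures are 0.275 SD and about 44%.

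Cost: revised wording and some extra analysis, no extra patients, and possibly a slightly wider interval. The remedy relies on a baseline resilience score. The readable text does not state that one is collected, so this must be confirmed, and if none is planned it would have to be added.
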